**Methods:**

Patients will be randomised 1:1 to either Treatment as Usual (control arm) or Treatment as Usual plus STABILISE intervention (intervention arm). Follow up points will be at 14, 30 and 52 weeks post eligibility confirmation, with 30 weeks as the primary end point. We aim to recruit 60 individuals meeting diagnostic criteria for a Bipolar Spectrum Disorder, and reporting ongoing bipolar symptoms (low mood or mood instability) outside of a manic or severe depressive episode. Feasibility and acceptability will be examined through recruitment and retention rates, completion rates for the candidate primary outcome measures (PHQ9, ALS-SF, QoL.BD and BRQ) and feedback from participants on their experience of study participation and therapy. Proceeding to a definitive trial will be indicated if the following criteria are met: (i) trial participation is deemed, or can be made, sufficiently safe; (ii) recruitment rate indicates that larger-scale recruitment would be feasible (recruitment rate of at least two participants per month within at least one site, with mitigation plan if overall target sample size not met); (iii) for candidate primary outcome measure follow up data is available at 30 weeks from at least 75% of participants, or from between 55 and 74% with clear plan for improvement.

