Overall safety of intervention and trial procedures as determined by TSC and sponsor^a^	Cannot be made sufficiently safe for use in a definitive trial		Can be made sufficiently safe following modification		Sufficiently safe for use in a definitive trial	
Mean recruitment rate per site over 15 months	< 2 participants per month at both sites		< 2 participants per month at one site and target sample size not reached, with clear plan for improvement		≥ 2 participants at both sites OR < 2 participants at one site but overall target sample size reached^b^	
Outcome measure completion at 30-week follow-up point (completion of candidate primary outcome measure at primary end point)	< 55% of participants		Between ≥ 55 and < 75% of participants, with clear plan for improvement		≥ 75% of participants	
Level of completion of intervention (defined as attending at least 6 therapy sessions)^c^	< 50% of participants		50–89% of participants, with clear plan for improvement		≥ 90% of participants	

Red: Do not progress to the main trial (unless TSC agree exceptional circumstances and a mitigation plan is present); Amber: Progress if action plan to mitigate problems can be determined and agreed with the Trial Steering Committee (TSC); Green: Progress directly to the main trial

^a^Subsequent to reviewing information on adverse and serious adverse events arising during the trial

^b^To allow for a situation in which recruitment systems require a lead-in period at a site before becoming optimized, and this optimization period can then be accounted for in planning for a definitive trial

^c^Information will be collected on reasons for discontinuation to inform plan for enhancing retention in intervention and/or refinement of the estimand for a definitive trial [28]

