### Design

This feasibility study has a two-arm randomised parallel controlled trial design. Participants will be randomised on a 1:1 ratio to Treatment as Usual (TAU) only (control arm) or TAU plus STABILISE programme (intervention arm). Outcome measures will be completed at baseline and at three follow-up points: 14, 30 and 52 weeks post study entry. We have selected 30 weeks as the primary end point to allow this to be immediately following the intervention period. The study takes a mixed-method approach whereby evaluation of therapy acceptability and potential impact is explored both qualitatively and quantitatively.

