### Sample size

A total of 60 individuals will be recruited (target *n* = 30 in Devon, and *n* = 30 in Avon & Wiltshire). A sample size of 60 participants allows estimation of loss to follow-up within ± 12 percentage points, assuming 20% attrition, and is sufficient to estimate the standard deviation in the candidate primary outcome measures [35, 36].

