## Data analysis

### Statistical analyses

Given the feasibility design, data analysis will focus on a descriptive analysis of the feasibility objectives of the study. We will report recruitment rates (average number of participants recruited per month) overall and by site. Retention and completion of outcome measures at follow-up timepoints will be reported as numbers and percentages, overall and by each treatment group. Participant characteristics at baseline will be reported descriptively for each treatment group, using mean (SD) for continuous variables, and percentages for categorical variables.

Outcome measures will be reported descriptively for each treatment group at baseline and at each post-randomisation follow-up, i.e. 14, 30 and 52 weeks. For 30- and 52-week follow-up data, the between group mean differences for continuous variables (intervention minus control group) will be reported with a 95% CI. The between group mean difference will be derived from a linear regression model, which will include treatment group as a fixed effect and will also adjust for study site and use of medication for BDs (factors used in the randomisation procedure). The feedback questionnaire will be reported descriptively for those items that relate to the STABILISE + TAU group only; the overall satisfaction item will be reported descriptively by treatment group and with a between group mean difference and 95% CI (using a linear regression model as for the clinical outcomes).

Given the feasibility nature of the trial, all participants will be analysed according to their randomised group irrespective of treatment actually received (intention to treat principle). Analyses will include observed data only; no imputation of missing outcome data will be performed. To explore potential mechanisms of missingness, we will report the mean (SD) for baseline PHQ-9 and GAD-7 for participants with and without completion of all four potential primary clinical outcome measures at 14 weeks, overall and by treatment group.

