## Anticipated risks and benefits

The administration of a novel therapeutic intervention raises the potential of risk to those in the trial, as well as potential benefit. We believe that the intervention is unlikely to pose significant risks: the approach is an adaptation of two widely used existing therapies (Behavioural Activation and Dialectical Behavioural Therapy), both of which have been delivered previously by our team to people with bipolar disorder in case series and trial contexts with no significant concerns about therapy safety resulting [18, 25]. We are currently completing a case series evaluation of the STABILISE approach: at the time of writing all 12 participants have completed the acute phase of therapy with no significant concerns arising regarding the safety of the intervention. Reactions to therapy will be monitored by therapists and within clinical supervision and standard operating procedures relating to monitoring and reporting adverse events will be followed.

In this study, participants are allocated at random to receive either TAU, or TAU plus the novel intervention. Therefore, there is a risk that a participant may be disappointed by allocation to the former arm. The inclusion of a treatment as usual comparator arm is necessary in order to address some of the feasibility aims (to establish the acceptability of procedures to be used in a definitive trial, including randomisation). Participants will be informed of the nature and purpose of the randomisation element. They will be called by an unblinded member of the study team to inform them of their allocation; their response to this will be monitored including the offer of a follow-up call the following day. Participants in both arms will be directed towards sources of support in the local community and nationally. It will be made clear to those in the usual care arm that whilst participants currently receiving psychological therapy for bipolar disorder will not be eligible to join the study, no restrictions are placed on the treatments that participants can choose to access outside of the study whilst they are a part of it. Because the treatment is experimental, it is not currently planned that it will be routinely offered to trial participants following study completion.

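### The 30-week completion criterion in Table 1 pools the arms, so the row can be Green while one arm is in the row's own Red range

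*Protocol article*

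**What the plan says.** In the protocol article, Objectives, Table 1, the third row is headed "Outcome measure completion at 30-week follow-up point (completion of candidate primary outcome measure at primary end point"). Its Green band is "≥ 75% of participants" and its Red band is "< 55% of participants"; the range between is Amber and needs a clear plan for improvement. The table note says that Green means going straight on to the main trial. Abstract criterion (iii) uses the same denominator: "follow up data is available at 30 weeks from at least 75% of participants". No arm is named in either place.

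Design: "Participants will be randomised on a 1:1 ratio to Treatment as Usual (TAU) only (control arm) or TAU plus STABILISE programme (intervention arm"). Sample size: "A total of 60 individuals will be recruited".

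Statistical analyses: "Retention and completion of outcome measures at follow-up timepoints will be reported as numbers and percentages, overall and by each treatment group". The same section limits outcome analyses to observed data without imputation. It compares baseline scores of completers and non-completers by arm, but at 14 weeks.

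The section on randomisation and blinding states that participants cannot be blinded. Of allocation to treatment as usual (TAU), Anticipated risks and benefits says that "there is a risk that a participant may be disappointed by allocation to the former arm". The Adverse events section notes that intervention participants have more contact with the study team because they attend therapy.

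**The concern.** The row is there to show whether a definitive trial would obtain usable primary outcome data at 30 weeks. For a comparison based on observed data, unequal loss between arms can do as much damage as a high total loss. A pooled percentage cannot tell the two apart.

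Unequal loss is a credible risk here. Participants know their allocation, the protocol recognises that TAU allocation may disappoint, and only one arm has regular therapist contact. No other row of Table 1 covers follow-up in the TAU arm: session attendance can only concern the intervention arm, and the safety and recruitment rows do not address retention. At stake is whether marked one-sided loss would oblige the team to produce a plan before this row is passed.

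**Working it through.** **Inputs.** N = 60 (Sample size); 1:1 allocation (Design); Green at 75% or more and Red below 55% (Table 1); 20% assumed attrition (Sample size). Exactly 30 per arm is an assumption, because minimisation with a random element need not give 30/30. The true completion rates by arm used below are also assumptions; the protocol gives none.

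**The plan's own figure.** The Sample size section states precision of ±12 percentage points for loss to follow-up at 20% attrition. For 12/60 lost:
- Wald: 1.96 × √(0.2 × 0.8 / 60) = 0.101, or ±10.1 points
- Wilson: 11.8% to 31.8% (−8.2/+11.8)
- Exact: 10.8% to 32.3% (−9.2/+12.3)

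The stated 12 agrees with the wider side of the Wilson or exact interval, so it reproduces. It refers to the whole sample. For one arm of 30, the Wald half-width is 1.96 × √(0.2 × 0.8 / 30) = 0.143, or ±14.3 points.

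**Splits that just reach Green.** 0.75 × 60 = 45 completers. The 55% line in an arm of 30 is 16.5, so 16 or fewer is below it and 17 or more is not.

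| Split | Completion by arm | Gap (points) | Lower arm below 55%? |
|---|---|---|---|
| 23+22 | 77% / 73% | 3 | no |
| 27+18 | 90% / 60% | 30 | no |
| 28+17 | 93% / 57% | 37 | no |
| 29+16 | 97% / 53% | 43 | yes |
| 30+15 | 100% / 50% | 50 | yes |

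**Probability that the row is Green.** Let A ~ Bin(30, p₁) and B ~ Bin(30, p₂), independent, and sum P(A = a)·P(B = b) over all pairs that satisfy each rule:
- Pooled rule: a + b ≥ 45
- With floor: a + b ≥ 45 and min(a, b) ≥ 17
- With 20-point limit: a + b ≥ 45 and |a − b| ≤ 6 (20% of 30)

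| True completion | Pooled | With 55% floor | With 20-point limit |
|---|---|---|---|
| 80% / 80% | 0.869 | 0.869 | 0.842 |
| 90% / 75% | 0.953 | 0.952 | 0.734 |
| 90% / 65% | 0.746 | 0.733 | 0.319 |
| 90% / 60% | 0.571 | 0.547 | 0.162 |
| 95% / 60% | 0.755 | 0.677 | 0.082 |
| 95% / 55% | 0.572 | 0.466 | 0.030 |

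The chance that the row is Green with an arm below 55% is the pooled column minus the floor column: 0.755 − 0.677 = 0.078 at 95%/60%, and 0.572 − 0.466 = 0.106 at 95%/55%. The chance that it is Green with half or more of one arm missing (15/30 or fewer completing) is 0.0015 at 90%/65% and 0.017 at 95%/60%.

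**A 75% bar in each arm.** This needs 23/30 in both arms, since 0.75 × 30 = 22.5. At 80%/80% the probability of Green falls from 0.869 to 0.579.

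**The case against.** The strongest case for the plan is that a pooled criterion fits its purpose. The sample-size rationale is about overall loss at n = 60, and objective (iv) speaks of data completeness at follow-up without splitting it by arm. There is no misstatement or contradiction. Several retention measures apply to both arms: a £20 honorarium at four points, a tailored procedure for non-response, a call about allocation with the offer of another next day, and a bespoke support plan. The disappointment is described as a risk, not as something expected. The TSC also holds the data-monitoring functions and could act on any imbalance it saw.

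All of this stands, and it limits the point. Two stronger readings are tempting, and the documents support neither:
- **That differential drop-out would be hidden.** Statistical analyses commits to completion by treatment group at the follow-up timepoints, so it would be visible.
- **That the whole trial could be Green with half of one arm missing.** This is one row of four; safety, recruitment and intervention completion are judged as well. Half of one arm missing with exactly 45 completers also requires complete follow-up in the other arm, and the event is rare in the scenarios above.

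What the objection does not answer is that a figure in a results table differs from a pre-specified rule that requires action. Nothing says how by-arm completion is to be weighed, and the planned missingness comparison by arm is at 14 weeks, not at the 30-week primary end point.

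**Conclusion.** The point holds as a gap in the decision rule. The 30-week completion row can be Green, with no improvement plan required, while one arm is in the range that the same row calls Red for the whole sample (29+16, 30+15) or far below the other arm (27+18). By-arm completion is reported but does not affect the row.

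The size is moderate. A Green row with an arm below 55% has probability 0.078 at true completion of 95%/60% and 0.106 at 95%/55%, and is negligible when both arms are truly 80%. A Green row despite a true gap of 25 to 40 points is much more likely (0.57 to 0.76 in the scenarios shown). These figures rest on 30 per arm, independent completion and assumed true rates. This is a cheap improvement to the progression criteria, not the correction of an error.

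**What to change.** In the 30-week row of Table 1 and in abstract criterion (iii), keep the overall bands and add: Green also requires that neither arm is below 55%, and that the TSC has reviewed 30-week completion by arm. If overall completion is at least 75% but an arm is below 55%, or the TSC judges the imbalance material, the row is Amber and an arm-specific retention plan is required.

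Both parts are needed. The floor uses the row's own Red line and costs nothing at 80%/80% (0.869 either way), but it catches only extreme loss: at 90%/65% it moves P(Green) only from 0.746 to 0.733. The TSC review covers splits such as 27+18.

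A fixed 20-point limit on the difference should be optional. It detects far more one-sided loss, but 20 is a judgement that no figure in the protocol supports. It also lowers P(Green) from 0.95 to 0.73 when true completion is 90% and 75%, where both arms meet the 75% bar. With that limit the 55% floor would be redundant: at least 45 completers and a difference of at most 6 already imply at least 20/30 in each arm.

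The cost is a short amendment, with sponsor and regulatory approval if it counts as substantive, and a slightly higher chance of Amber, which requires only an agreed plan. The data are already to be tabulated by arm. Recruitment was scheduled for April 2024 to June 2025, so the rule should be fixed before by-arm 30-week completion is seen.

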## Method

This feasibility study protocol is reported according to the SPIRIT 2013 statement.

### Design

This feasibility study has a two-arm randomised parallel controlled trial design. Participants will be randomised on a 1:1 ratio to Treatment as Usual (TAU) only (control arm) or TAU plus STABILISE programme (intervention arm). Outcome measures will be completed at baseline and at three follow-up points: 14, 30 and 52 weeks post study entry. We have selected 30 weeks as the primary end point to allow this to be immediately following the intervention period. The study takes a mixed-method approach whereby evaluation of therapy acceptability and potential impact is explored both qualitatively and quantitatively.

### Setting and participants

The trial will be conducted across two sites in the U.K. (an NHS mental health Trust, and a specialist NHS outpatient psychological therapies service based at the University of Exeter) with participants allowed to be recruited from primary care services, secondary care mental health services and via self-referral. For details of study sites please see: https://www.isrctn.com/ISRCTN18207465.

Eligible participants will be aged 18 or over with a diagnosis of Bipolar Disorder (I, II, Other Specified Bipolar Disorder) or Cyclothymic Disorder, according to DSM-V [29] criteria assessed using the Structured Clinical Interview for DSM-V (SCID-5 [30]). Participants must report either current bipolar mood instability, defined as a score of at least 1.3 on the depression-elation subscale of the short form Affective Lability Scale (ALS [31]), or presence of at least mild depressive symptoms, defined as a score of at least 5 on the Patient Health Questionnaire (PHQ-9 [32]: see Additional File 1 for details of measures used). They must also be willing to engage in psychological therapy that focuses primarily on psychological work addressing ongoing bipolar symptoms or their impact on functioning, and must be able to attend regular therapy sessions. Participants must have sufficient competency in English such that study measures can be completed without the need for translation (to preserve the measure properties), have completed the intake measures, and be registered with a General Practice in the study site catchment area.

Participants will not be included if they are currently experiencing a manic episode (assessed using the SCID-5) or severe major depressive episode (assessed using the SCID-5; the Hamilton Depression Rating Scale [33], an established, validated measure of current depression symptoms, will be used with participants who meet criteria for a current depressive episode to establish severity). We will not include participants with current substance dependence according to The International Classification of Diseases, 11th revision (ICD-11 [34]) criteria; ICD-11 rather than DSM-V criteria are used to permit assessment of substance dependence rather than the broader construct of substance use disorder. Participants who present a risk of harm to themselves or others that cannot be safely managed in a community outpatient setting, will not be included. Receiving multiple, separate psychological interventions for BD simultaneously is not generally considered clinically advisable, therefore participants will not be eligible for the study if currently receiving a psychological intervention for BD at the point of study intake.

Medication status will not serve as an exclusion criterion but will be recorded. In both conditions participants will continue to be able to access routine care.

### Sample size

A total of 60 individuals will be recruited (target *n* = 30 in Devon, and *n* = 30 in Avon & Wiltshire). A sample size of 60 participants allows estimation of loss to follow-up within ± 12 percentage points, assuming 20% attrition, and is sufficient to estimate the standard deviation in the candidate primary outcome measures [35, 36].

### Randomisation, concealment of allocation and blinding

Participants eligible for the study will be randomised on a 1:1 ratio (with minimisation by trial site and medication status [currently prescribed medication for depression or Bipolar Disorder versus not prescribed such medication]) to Treatment as Usual (TAU) [control arm] or Treatment as Usual plus STABILISE programme (TAU + STABILISE) [intervention arm]. Allocation concealment during the randomisation process will be achieved through use of a validated password protected online randomisation tool programmed and hosted by the Exeter Clinical Trials Unit. The first six participants will be allocated using simple randomisation and then the minimisation procedure will commence, maintaining a stochastic element to the algorithm to allow concealment to be maintained. The minimisation algorithm will take account of the allocations of the first six participants. Participants will be enrolled into the randomisation system and informed of their allocation by an unblinded researcher.

Given the nature of the intervention, blinding of participants to allocation is not possible. Follow-up assessments will be conducted by separate researchers who are unaware of the participant’s allocation. At follow-up, outcome assessors will be instructed to maintain blinding by reminding participants not to reveal their allocation during the contact. Outcome assessors will be asked to indicate at follow-up which treatment they believe the participants received, allowing us to test blinding status and analyse any correlation with outcome. The outcome assessors’ blind will be maintained as far as possible; they will be deliberately unblinded only in exceptional circumstances where knowledge of the treatment arm is deemed essential to their management of the participant (e.g. certain Serious Adverse Events). Instances of deliberate or accidental un-blinding will be recorded; future data collection from that participant will be carried out by a member of the team who remains blinded. An unblinded researcher will collect data from participants that pertain to their allocation (qualitative and quantitative feedback about their experience of the study and of the therapy). All other members of the study team will be unblinded other than those performing statistical analyses on the data (health economist and statistician). Statistical and economic analyses will be performed by a statistician and health economists who are blinded to participant allocations.

### Recruitment

Participants will be identified from local NHS services including but not limited to primary care psychological therapies services, General Practices, secondary care mental health teams, early intervention services and secondary care psychological therapies services. In addition, advertisements for the study will be placed in healthcare settings, public places and distributed through traditional and social media, and third sector organisations. Potential participants who are interested in the study will be given the choice of contacting the researchers directly by telephone, email or post or completing a ‘permission to contact’ form which can be passed to the research team by their clinician or sent directly to the study team by the participant.

After a potential participant contacts or is referred to the study, a member of the research team will answer any initial questions and have an initial discussion about the study if the person wishes. Following receipt from the participant of a completed form gaining their consent for contact and an initial telephone screening call (‘permission to contact’ form), the researcher will arrange a time to complete this with the participant. In the screening call, the researcher will go through the inclusion and exclusion criteria with the participant, to give an indication of the likelihood that the participant will be eligible. Those likely to be eligible and willing to continue will be invited to the intake appointment.

At the appointment, the researchers will take written consent if the participant wishes to proceed and conduct the eligibility assessment. If the potential participant is eligible to partake in the study, is fully informed and has consented to participate, then they will be enrolled into the study.

Participants will be offered an honorarium of £20 for their participation at four points in the study: the intake assessment and the 14, 30 and 52 week follow-up points.

